## Abstract

**Background**: There is no cure for mitochondrial diseases which manifest in numerous ways including fatigue, muscle weakness, and exercise intolerance. Medical treatment varies and focuses on managing symptoms. Photobiomodulation (PBM) can decrease mitochondrial damage thereby increasing energy production and decreasing cell death. This pilot study will apply PBM to people with mitochondrial encephalomyopathy, lactic acidosis, and stroke-like episodes (MELAS) to examine the safety of application, and if changes occur in symptoms and signs after cross-over application/withdrawal of a sham or active PBM treatment including a two-week period of washout. **Methods**: This study is an exploratory, prospective series N-of-1 (single patient) studies. The protocol is guided by the CONSORT extension for reporting N-of-1 trials (CENT 2015), chosen due to the rarity of mitochondrial diseases, the fluctuating symptomology, and heterogeneity of the clinical presentation. The primary outcome is patient-reported fatigue assessed using the Checklist of Individual Strength and with concomitant evaluation of safety. Secondary measures are of depression, anxiety and stress, sleepiness, physical activity, blood lactate and creatine kinase, physical measures of sit-to-stand, and heel raise capability. Mitochondrial function will be evaluated using hydrogen magnetic resonance spectroscopy for lactate. PBM will be a participant-administered, home-based therapy using a multiple diode flexible array (BeniLight iLED-Pro Multi-Wave Multi-Pulse belt; 465 nm, 660 nm, 850 nm; average irradiance 5.23 mW/cm^2^; total joules: 770.1 J/treatment, all sites; 5 KHz; 20% duty ratio) over the anterior thigh muscles, posterior calf muscles and abdomen for 10 min to each site, three times/week. The safety of the intervention will be assessed. Descriptive statistics, causal analyses of time series data and dynamic modelling will be applied as relevant to the variables collected. Hydrogen magnetic resonance spectra will be acquired and averaged to obtain the content of the targeted hydrogen levels. **Discussion**: The study will provide guidance on whether and how to progress to a larger, randomised cohort study with sham control.

## 1. Introduction

Primary mitochondrial diseases (MD) are the most common group of inherited metabolic diseases and are characterized by impairment of the mitochondrial electron transport chain. The presentation of MD is complex, and diagnosis can be challenging due to the multi-system nature of these conditions. There is no curative treatment for MD, and management is supportive [1]. Although there are a number of mitochondrial and nuclear pathogenic variants associated with primary mitochondrial disease, the m.3243 A>G mutation in the *MT-TL1* gene encoding the mitochondrial tRNA^Leu(UUR)^ is one of the more common variants identified [2,3], and is associated with two primary, often overlapping syndromes:Mitochondrial encephalomyopathy, lactic acidosis, and stroke-like episodes (MELAS) primarily affect the nervous system and muscles. MELAS presents in children or young adults as recurrent episodes of encephalopathy, myopathy with reduced exercise tolerance and fatigue, migraines, seizure disorder, and focal neurological deficits.Maternally inherited diabetes and deafness (MIDD) is characterised by mitochondrial diabetes, hearing impairment, and maculopathy but can have other clinical manifestations and clinical overlap with MELAS.

This study focuses on MELAS which is progressive and life-limiting. Most individuals reportedly survive about 17 years [4] following the onset of symptoms such as seizures or other problems of the nervous system. There is an urgent need for the exploration of new treatment modalities to manage symptoms and improve the quality of life in people affected by MELAS. We aim to explore the notion that photobiomodulation (PBM; light therapy) activates mitochondria and relieves symptoms and signs of mitochondrial disease-related fatigue.

## 2. Background

MELAS is a rare, neurodegenerative, multisystem mitochondrial disease [2]. The function and survival of most mammalian cells are critically dependent on mitochondria. Although classically known to be the “powerhouse” of the cells, mitochondria are critical for other functions, including regulation of immunity, calcium balance, stem cell regulation, biosynthesis of hormones, cell death and renewal (autophagy/apoptosis), and cell metabolism [5].

Mitochondrial DNA (mtDNA) is maternally inherited and comprises 37 genes, encoding 13 proteins essential for oxidative phosphorylation (22 transfer RNAs and two ribosomal RNAs). However, the majority of the approximately 1500 proteins required for mitochondrial function are encoded by nuclear genes and as such are subject to classical Mendelian inheritance [6]. The most common pathogenic variant, known as m.3243 A>G was found to be carried by one in 500 community-based Australians [2]. The prevalence of all forms of childhood-onset (<16 years of age) MD has been estimated to range from 5 to 15 cases per 100,000 individuals [2].

A notable feature of mtDNA is heteroplasmy, the coexistence of multiple mtDNA variants within a single cell. The proportion of mutated to wild-type mtDNA can vary across different tissues, influencing disease manifestation [5]. The manifestations of mitochondrial disease are contingent on both the heteroplasmic load as well as the energy requirements of the tissue/organ systems involved, known as the “threshold effect” [7]. Due to mitotic segregation, the mutation load can change between different generations of cells and thus the threshold effect may vary over time resulting in variability in presenting features [6]. Symptoms of MELAS are most prominent in tissues with the highest energy requirements, including muscle [5]. Patients may present with fatigue, exercise intolerance, myalgia/cramping as well as an increased risk of rhabdomyolysis [8]. These muscle-related factors may severely impact quality of life, often out of proportion with clinical findings.

As there is no cure for MELAS, current standard treatment focuses on supportive management, including therapies for existing complications (e.g., cochlear implants, treatment of diabetes, cardiac failure, arrhythmia, migraines, or seizures), guidance on medications to avoid (e.g., sodium valproate, metformin, aminoglycoside, and other ototoxic medications), genetic counselling, family planning and cascade testing as well as instituting surveillance for timely management of potential complications [1]. There is minimal evidence for the use of a mitochondrial cocktail, including antioxidant therapy such as coenzyme Q 10 [1], but these therapies are sometimes trialled. The current clinical guidelines on physical exercise in mitochondrial disease [1] include recommendations for graded regular physical activity; for those without medical contraindications, moderate-intensity aerobic exercise at 70% of the person’s maximum heart rate to improve baseline levels of exercise; tailored exercise programs following consultation with exercise physiologist/physiotherapist/sports medicine therapist. Evidence to support resistance/concentric and high-intensity interval training in MD is limited [1]. We seek to add to the toolkit of therapies to address MELAS-related fatigue.

Although recently proposed by other authors as a therapy for MD [9], at the time of writing no published studies have investigated PBM as an effective method for managing symptoms of MELAS. We provide an overview herein, to understand why we think that PBM may be a useful adjunct in the clinical management of people with MELAS.

### The Proposed Role of PBM in MELAS

Mitochondrial disorders are primarily caused by dysfunctions in the oxidative phosphorylation (OXPHOS) system, which is crucial for ATP production in cells [8]. OXPHOS is a cellular process that generates energy in the form of adenosine triphosphate (ATP). Gorman and colleagues have described OXPHOS as a vital metabolic process occurring in the mitochondria of cells [10] and summarise the process as follows. OXPHOS requires the transport of electrons to molecular oxygen by the mitochondrial respiratory chain (known as the electron transport chain) involving four multi-subunit complexes (complex I to complex IV) and two mobile electron carriers known as coenzyme Q10 (or coenzyme Q or CoQ) and cytochrome *c*. The respiratory chain generates a transmembrane proton gradient harnessed by complex V (known as ATP synthase) to synthesize ATP. The electron transport chain is a substantial source of often deleterious reactive oxygen species (ROS). Although several enzymes, including superoxide dismutase (SOD) in mitochondria, are involved in ROS disposal, excessive ROS might have a role in the pathogenesis of MD [10]. The m.3243 A > G gene mutation causes translational defects that disrupt the OXPHOS function of the electron transport chain [11]. People with MELAS often exhibit a marked decrease in complex I activity, as evidenced by reduced enzymatic activity in muscle biopsies and fibroblasts [12].

There are a number of proposed mechanisms of action for PBM in the setting of mitochondrial dysfunction [13,14] as summarised here:

PBM acts via mitochondria displacing nitric oxide (NO) from the respiratory chain and increasing levels of adenosine triphosphate (ATP) with modest increases in superoxide dismutase (SOD) activity considered to be beneficial. PBM can produce ROS in normal cells but when used in oxidatively stressed cells, ROS levels and oxidative stress are lowered. The described changes activate transcription factors resulting in changes in gene expression and subsequent downstream production of chemical messengers implicated in the cellular improvements seen following PBM exposure clinically.

In vitro studies of the effects of PBM on mitochondrial activity have utilised various wavelengths (visible and invisible light), irradiances (power output per unit area of treatment), and fluences (photonic energy). Indeed, PBM has been found to increase the activity of respiratory chain complexes in an apparent dose- and time-dependent manner [15]. As defects in any one complex can influence other complexes [8], we propose that PBM may beneficially influence damaged mitochondria in people with MELAS. The best effects of PBM are likely to be in body tissues with increased numbers of mitochondria (such as muscles) using a combination of red, blue, and infrared wavelengths (e.g., [16]).

As pre-conditioning prior to exercise, PBM has moderately strong evidence for increasing the time to exhaustion [17] and low to moderately strong evidence for reducing signs of muscle fatigue in healthy subjects [18] but also in people with chronic obstructive pulmonary disease [19]. PBM significantly reduced muscle fatigue across a range of indicators including reduced ratings of perceived exertion (beneficial effect); increased electromyographic fatigue index (beneficial effect); and increased a range of muscle indicators including peak torque, time to peak torque, total work, average power, and average peak torque (beneficial effects), with significant differences between both PBM and placebo conditions [20]. In that study, when compared to a placebo, PBM applied before exercise improved indicators of muscle performance. A change in absolute deoxyhaemoglobin and myoglobin (deoxy[Hb + Mb]) after a PBM exercise pre-conditioning protocol was suggestive of muscle oxygenation and metabolism changes potentially by increasing local matching of bulk and microvascular oxygen delivery relative to muscle oxygen utilisation [21]. These effects may have been mediated by mitochondrial activity, but the study was not devised to test that effect.

Taken together, the literature suggests that muscle fatigue and poor performance are mitigated using PBM. We seek to test whether the PBM effects summarised above might be possible in MELAS, which is expressed clinically as muscle weakness and fatigue as a result of mitochondrial damage. The study rationale is that PBM stimulates mitochondrial biogenesis limiting the effects of muscle fatigue. We propose the mechanism of the PBM effect in MELAS is via enhancement of complex I activity [15] thereby improving fatigue, other measured symptoms/signs, and blood test results. We will undertake exploratory feasibility work to determine if mitochondrial function is a consequence of PBM when applied in people with MELAS. We start by testing for safety and any effects in a series of N-of-1 studies of people with MELAS under the supervision of the patients’ treating doctor (Author LP).

## 3. Objectives

Our primary objective is to determine if combined red (660 nm), infrared (850 nm), and blue (465 nm) wavelengths of PBM applied using an array of multiple light emitting diodes (LED belt) is safe and reduces patient-reported fatigue as measured using the Checklist of Individual Strength (CIS) in people with MELAS.

The secondary objectives are as follows:

‐To determine if fatigue-related factors such as depression, anxiety, stress, and sleepiness are influenced by the application of PBM in people with MELAS.‐To determine if physical strength and activity changes in people with MELAS after PBM application to the large muscles of the lower limbs and the anterior abdomen.‐To determine if imaging using proton (^1^H) MR spectroscopy can show any change in mitochondrial activity in gastrocnemius muscles of the legs in people with MELAS.‐To determine if plasma creatine kinase (CK) and lactate are influenced by PBM application to the large muscles of the lower limbs and the anterior abdomen in people with MELAS.‐Based on outcomes, determine the feasibility of taking this research to the next phase as a larger clinical study.

## 4. Materials and Methods

### 4.1. Study Design

This study is an exploratory, prospective series of N-of-1 studies guided by the CONSORT extension for reporting N-of-1 trials (CENT 2015) [22]. We have chosen this method due to the rarity of MDs, their fluctuating symptomology, and the heterogeneity of clinical presentation. N-of-1 studies test the efficacy of an intervention using one or a small number of patients by sequentially applying and withdrawing the intervention [23]. The simplest of such study designs is an A-B-A design where A is ‘no treatment’ and B is the intervention being studied. Continuous measurement of chosen outcomes occurs through each of the stages.

The PBM parameters will be standardised in all study participants, following an A-B-A-C design (Figure 1) as follows:
‐A = no intervention observational period: Daily patient diary (visual analogue scale; VAS) of fatigue and pain to understand usual (baseline) behaviour of fatigue and pain symptoms, to compare with any change during/after intervention. Fourteen data points will be obtained in each non-intervention period. In this study, the repeated “A” period will also serve as a washout period after the sham phase, to account for any placebo response.‐B = sham intervention period: Daily patient diary (VAS) of fatigue and pain symptoms will be assessed. Fourteen data points will be obtained. We have included a sham phase in this series of N-of-1 trials to satisfy the requirement to understand if there may be a placebo element to the initial application of light. To reduce the burden on participants, we have chosen a 2-week sham period which is expected to demonstrate any change from baseline. The following A phase will assist in determining the durability of any placebo effect that we may need to consider in a future study.‐C = active intervention (PBM application) period: Twice-weekly patient diary of fatigue and pain symptoms will be assessed. Sixteen data points will be obtained over an 8-week period of treatment. The intervention period is based on exercise science findings demonstrating increased mitochondrial activity with endurance exercise [24] and mitochondrial biogenesis after 4–6 weeks of interval training in healthy individuals [24,25]. If PBM influences muscle mitochondrial function, we expect that 8 weeks of home-based intervention may be required to demonstrate effects in a clinical population that would normally struggle to participate in exercise programs.

As the latency, variability, and magnitude of the outcome of PBM in people with MELAS is not known, we have chosen to adjust the length of each phase based on the likelihood of the following: (a) gathering sufficient data points to observe an effect, and (b) garnering an effect with the study intervention.

### 4.2. Participants

Three patients from the Queensland Diabetes and Endocrine Centre (QDEC) who have been medically diagnosed with MELAS and where their primary symptom is fatigue. Participants will be over the age of 18 years and of either sex. Patients will be consented into the study non-concurrently. Patients will be ineligible to take part in the study if they have any contraindications or precautions to magnetic resonance spectroscopy or PBM (e.g., light sensitivity, pregnancy, recent history of cancer in area to be treated), uncontrolled psychiatric condition within the last 3 months, inability to comply with or undertake physical tests required for the study.

Consenting patients will receive a unique study code by which their data will be tracked. All study data will be de-identified at the conclusion of the study so that it becomes unidentifiable. Data collection tools will use both patient participant name and study code to permit tracking of data and extraction of relevant health information from medical records.

### 4.3. Intervention

We will assess the clinical response to the application of combined wavelengths of PBM using the BeniLight iLED-Pro Multi-Wave Multi-Pulse PBM device (https://benilight.com/products/benilight-iled-pro, accessed on 21 January 2025) which is an FDA-approved class 2 medical device. The light belt device is 385 mm × 85 mm in size. When programmed in active treatment mode, it emits 465 nm (visible blue), 660 nm (visible red), and 850 nm (infrared invisible) light via LEDs, and a custom lens package with >15° viewing angle; 5.23 mW/cm^2^ irradiance; 5 KHz frequency @20% duty ratio delivering a total fluence/treatment of 770.1 J. During the sham treatment period the LED array of the belt will be disconnected internally from the controller, so all functions display as required but with no output from the device.

The device will be self-applied by participants in the home setting, in contact with the skin over the anterior thigh muscles, posterior calf muscles and abdomen for 10 min at each site. The large quadriceps and gastrocnemius muscles have been chosen as these muscles are most likely to be affected by peripheral fatigue. The abdominal site has been chosen due to our recent (unpublished) findings that abdominally applied PBM has an effect on the gut–brain axis influencing factors associated with central (mental) fatigue.

Depending on the patient’s wishes, the scheduling of the treatment is modifiable, as follows:
‐Six days/week with one day rest each week, alternating each application site (e.g., ten minutes to the abdomen on Monday and Thursday, ten minutes to each thigh on Tuesday and Friday, and ten minutes to each calf on Wednesday and Saturday)

OR

‐Three days/week across all application sites (e.g., Monday, Wednesday, and Friday each week, the device is applied consecutively to the abdomen, the thighs, and calves for ten minutes at each site. The applications can be done in one sitting or spread across the day in separate ten-minute sittings).

The participant choice of application scheduling is permitted to fit in with the participants’ lifestyle but total PBM fluence and irradiance will be equivalent in both schedules.

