### 4.6. Research Ethics Considerations

The study has been ethically approved by the Mater Misericordiae Limited Human Research Ethics Committee (HREC/MML/108898). As this is an exploratory series of N-of-1 trials, there will be no randomisation of participants, and it is not considered essential in N-of-1 trials [22]. The order of intervention/withdrawal periods will not be randomised. Participants will be able to withdraw from the study at any time without a need for explanation. Where the participant requests withdrawal from the study, a request will be made for consent to use study data that has already been collected and permission to collect and use standard medical information for characterising the patient’s illness profile. No reference will be made in any publication or presentation that will allow the identification of a patient. The paper files and electronic files related to this study will be stored securely as per research compliance requirements. Once the study is completed, identifying data will be removed from all sources (redacted from paper-based forms and deleted from electronic forms) so that all data becomes unidentifiable. Imaging data will be stored using the patient’s unique identifying code on a secure cloud platform that is only accessible to the investigators.

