### 5.1. Limitations

As MR spectroscopy is expensive, our initial work is being done as a series of N-of-1 studies to establish the proof of concept. As a series of N-of-1 trials, it will not be possible to entirely exclude a placebo effect, but we have attempted to account for the effect by incorporating an initial sham phase into the study design. Equally, the small number of participants means the findings cannot be generalised. It is important to note that there are many statistical challenges related to N-of-1 trials including variability in patient responses, treatment-by-patient interactions, and missing data related to non-compliance with treatment. By maintaining weekly contact with participants, we expect to reduce the incidence of non-compliance with treatment.

The rationale we have taken for the choice in PBM parameters is based on a mix of theoretical underpinnings and published effects. In the absence of previous literature, dosing characteristics (duration and frequency of application, and duration of treatment protocol) are theoretical. The choice of the nominated red, blue, and NIR wavelengths is based on results from published in vitro and animal studies. Whether any of these factors translate into a human model of MD is unknown.

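### The sham belt is dark and the active belt glows blue and red, so Phase B cannot serve as the placebo reference for self-reported fatigue in Phase C

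*Protocol article*

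**What the plan says.** Section 4.3 of the protocol article describes the belt in both modes. In active mode "it emits 465 nm (visible blue), 660 nm (visible red), and 850 nm (infrared invisible) light via LEDs". In the sham period "the LED array of the belt will be disconnected internally from the controller", with the result that "all functions display as required but with no output from the device". On handling, the same section says: "The device will be self-applied by participants in the home setting, in contact with the skin".

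Section 4.1 fixes the sequence as A-B-A-C, with B the sham and C the active phase. It gives the purpose of the sham as "to understand if there may be a placebo element to the initial application of light". The second A phase is a washout and is meant to show how long any placebo response lasts. Section 4.6 confirms the fixed sequence: "The order of intervention/withdrawal periods will not be randomised".

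Section 4.4 makes patient-reported fatigue the primary outcome, measured with the Checklist of Individual Strength. Section 5.1 concedes that "it will not be possible to entirely exclude a placebo effect" and then says "we have attempted to account for the effect by incorporating an initial sham phase into the study design".

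**The concern.** A sham phase is useful as a placebo reference to the extent that it feels and looks like the active phase. Here the two differ in the most obvious feature of a light treatment, which is whether light can be seen. The outcome most exposed is the primary one, because fatigue is self-reported and open to expectation. There is no parallel group and no randomised order, so Phase B is the only placebo control in the design.

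The Abstract and Section 6 say the results will guide whether and how to move to a larger sham-controlled study, including its sample size. If a response to seeing the light is read as a PBM effect, two things carry forward: an effect estimate that is too large, and a sham method whose adequacy has not been shown.

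**Working it through.** The plan states no figure on this point, so there is nothing to reproduce. The check sets the sections side by side.

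**Inputs**

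| Feature | Phase B (sham) | Phase C (active) | Source |
|---|---|---|---|
| Light at 465 nm and 660 nm (visible) | absent | present | Section 4.3 |
| Light at 850 nm (not visible) | absent | present | Section 4.3 |
| Controller display | normal | normal | Section 4.3 |
| Who applies the belt | participant, at home | participant, at home | Section 4.3 |
| Position in sequence | always earlier | always later | Sections 4.1, 4.6 |
| Length | 2 weeks | 8 weeks | Section 4.1 |
| Diary | daily, 14 points | twice weekly, 8 × 2 = 16 points | Section 4.1 |
| Blood tests | none | at start and end | Section 4.4 |
| Treatment between two scans | none | first active session | Section 4.5 |

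**Step 1: what each phase contains.** Write the improvement in self-reported fatigue as a sum of parts:

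- r: response to the device, its display and the routine
- v: response to seeing the light
- p: effect of PBM itself
- t: everything due to order, length and visit schedule

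Taking r as the same in both phases, and t relative to Phase B:

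- Phase B = r
- Phase C = r + v + p + t
- C − B = v + p + t

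**Step 2: compare with the stated purpose.** Section 4.1 wants to know about a placebo element to the application of light, which is r + v. Phase B emits no light and so can inform only on r.

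**Step 3: the consequence.** If p = 0 and t = 0, then C − B = v. The whole response to the visible light is left in the contrast.

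**Step 4: what a cover can achieve.** Hiding the light in both phases moves v towards zero. It leaves t untouched, because the last five rows of the table still separate C from B. Even with perfect masking, C − B = p + t, so a difference could still not be assigned to PBM alone.

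**The case against.** The case on the other side has several parts, and some of it stands.

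- **Recognition on first use.** A reader might infer that participants will know the dark belt is a sham as soon as they switch it on. The article does not support that. B comes first, the controller displays normally, and there is no lit belt to compare with. Recognition by comparison can arise only in C, after the B scores are recorded. What participants are told in advance is not in the article. This stands, and it is why B can still show r.
- **The plan claims little.** The article does not say that participants are blinded, and it does not name C versus B as its estimand. Section 4.7 plans descriptive statistics, graphs and possible dynamic modelling, with pre-post effects explored for Phase C. This stands as a limit on the point. Even so, Section 5.1 offers the sham as the means of addressing placebo in a study whose subject is the active phase, and that use needs B to be comparable with C.
- **Placebo is already conceded.** Section 5.1 does hedge. But it attributes the difficulty to the N-of-1 format and presents the sham as mitigation. It does not say that the sham looks different.
- **Skin contact hides the light.** It may hide some. The article does not say it hides all, and participants place and remove the belt themselves.
- **A belief check may exist elsewhere.** A reader might infer that none is planned. A journal article can leave that to the full protocol, so silence here is no evidence either way, and the point does not rest on it.
- **Not every outcome is exposed.** Spectroscopic lactate, blood lactate and creatine kinase are not self-reported. The point is confined to self-reported outcomes.

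**Conclusion.** The concern holds in a limited form. Phase B may capture the response to device and routine, but it does not reproduce the visible light. It therefore cannot be the placebo reference for self-reported fatigue in Phase C, and the caveat in Section 5.1 does not tell the reader so. The stronger statement, that this sham captures no placebo response at all, goes beyond the documents.

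No number can be put on the bias. It equals v, for which the article gives no value. It is nil if participants respond no differently to a glowing belt than to a dark one, and otherwise as large as the difference in response. The conclusion assumes that some light is visible when the belt is placed, worn or removed, and that no masking measure in the full protocol already hides it.

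Because this is an exploratory series of three participants, with findings that Section 5.1 says cannot be generalised, this is a point to correct rather than a fatal one. It is best corrected before Phase B begins for each participant, since analysis cannot restore masking once it is lost.

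**What to change.** 1. **Mask the light in both phases.** Use the same opaque cover over the outer side of the belt in B and C, and also at the treatment session between scans in Section 4.5. The belt is strapped on and covered before it is switched on, and switched off before it is removed. Skin contact, sites, dose and schedule do not change.
2. **Ask about belief once.** After the last Phase C outcome is recorded, ask each participant which mode they think they had in each of the two phases. Asking at the end of B could alert them before C. Report the answers descriptively, since a late guess may also reflect perceived benefit.
3. **Reword Sections 4.1 and 5.1.** State that Phase B shows response to device and routine only. State also that a C-versus-B difference in self-reported outcomes is not attributed to PBM alone in any participant, because order, length and visit schedule differ too. If the cover is not adopted, name the unlit sham as a limitation.

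The cost is a cover for each of three participants, one line of instruction, one question covering both phases, and a few sentences of text. The downside is slightly more awkward home use, and masking may remain imperfect.
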